### Intervention

Diabetic patients will receive either 5g/d (2.5 g at breakfast and 2.5 g at dinner) of bitter almond gum powder (bitter almond gum, Flavinea Co, Iran) or maltodextrin powder (placebo) (Jiujiang Hurirong Trade Co, China) for 2 months. Participants will be instructed to use supplements with semi-solid food like yogurt or salad. Both bitter almond gum and maltodextrin powders are odorless and tasteless and will be provided in identical opaque packages. Study participants will be informed on how to take their supplements. Patients will be followed by phone calls twice a week to ensure compliance with the intervention and dietary and physical activity guidelines and receive reports of possible adverse events experienced following bitter almond gum consumption. Compliance will be assessed based on a self-administered checklist and used packages by each person. Also, a checklist will be provided for participants to mark after each consumption of the prescribed supplement to evaluate for cases of non-compliance. Adherence to the regular consumption of powders (bitter almond gum or placebo) will also be determined by counting packages, also at least 10% of the supplements as noncompliant participants and, consequently, excluded from the study. Participants will be free to withdraw from participation in the study at any time upon request. Withdrawal criteria will be as follows: (1) Any clinical adverse event or medical condition occurs that the patient’s continued participation in the study would not be in the best interest of her and (2) the patient meets a newly developed or not previously recognized exclusion criterion that precludes further study participation. When the study ends, the results will be notified to all participants by post and published on a public website.

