### Study design and participants

The proposed study is a randomized, triple-blind, placebo-controlled, parallel-group clinical trial with a superiority framework to deliver an intention to treat (ITT) to evaluate the efficacy of bitter almond gum on cardio-metabolic, immune-inflammatory, and oxidative stress biomarkers, as well as mental health, compared with a placebo in women with T2DM. The allocation ratio will be 1:1. The study will begin later this year, 2022. Women with T2DM will be recruited from clinics of the Tabriz University of Medical Sciences, Iran, through public announcement systems and doctor referrals. A trained nutritionist will be served to include participants until the target sample size is reached and the project supervisor will assign participants to intervention groups based on the randomization list. The research design is presented in Fig. 1. This clinical trial protocol is based on the Standard Protocol Items: Recommendations for Interventional Trials (SPIRIT) 2013 checklist (Additional file 1: SPIRIT checklist) [31]. The diagram of the study protocol and initial and ongoing participant recruitment is demonstrated in Table 1.

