### Eligibility of criteria

Women aged between 30 and 65 years and diagnosed with T2DM (fasting blood sugar (FBG) ≥126 mg/dl [32]) that satisfy the inclusion criteria will be recruited. The inclusion criteria will be considered as follows: diagnosed with T2DM at least 6 months, body mass index (BMI) > 25 and < 35 kg/m^2^, no weight changes during the last three months, use of glucose-lowering drugs (including sulfonylureas, glinides, biguanides, thiazolidinediones, dipeptidyl-peptidase 4 inhibitors, sodium-glucose transporter 2 inhibitors, alpha-glucosidase inhibitors, amylin mimetics, and incretin mimetic), dietary fiber intake of < 25 g per day, and propensity to take bitter almond gum supplement during the study. Patients will be excluded if they use insulin, glucocorticoids, laxatives, anti-obesity drugs, nonsteroidal anti-inflammatory drugs (NSAIDs), antidepressants, and antibiotics; take supplements including multivitamins, n-3 fatty acids, Ginkgo biloba, antioxidants, probiotics, and other prebiotics in the previous 3 months before the recruitment; have a history of weight loss or dieting in the last 6 months; have cancers and gastrointestinal, thyroid, heart, kidney, liver, lung, and infectious diseases; consume alcohol and smoke; and are pregnant or lactating.

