### Randomization and blinding

After obtaining the informed consent of the study participants, eligible subjects will complete a 2-week run-in period. During this time, patients will be requested to follow dietary and exercise advice according to recommendations for T2DM patients [33]. After the run-in period, the patients will be randomized to one of the two arms (bitter almond gum group or placebo group) in equal numbers, stratified by age and BMI. For stratified block randomization, random allocation software (RAS) will be used with block sizes of 2 and 4. Randomization will be performed by a third party that is not involved in this research. Block size will be concealed to all researchers until code-breaking. To enter a patient into the trial, one of the researchers will open the sequentially numbered sealed opaque envelopes. The study design is blinded to the main investigator, those who collect the data, the statistical consultant, and the participants.

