### Data management

The study progress, protocol, validity, and integrity of the info, also as ethical requirements, will occasionally be supervised by a clinical trial monitor. All participants will be encouraged to answer the questions honestly. To analyze the data of the participants who withdraw from this trial for any reason, the ITT analysis will be used. All participants will be followed up for 8 weeks after the treatment assignment.

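### Removing randomised women from the study on a package count conflicts with the intention-to-treat commitment and with 8-week follow-up of all participants

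*Protocol article*

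**What the plan says.** Four statements bear on who is followed and analysed.

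- **Study design and participants** describes a superiority trial analysed by intention to treat.
- **Data management** says: "To analyze the data of the participants who withdraw from this trial for any reason, the ITT analysis will be used". The next sentence adds: "All participants will be followed up for 8 weeks after the treatment assignment".
- **Intervention**, on adherence by package count: "also at least 10% of the supplements as noncompliant participants and, consequently, excluded from the study". The verb before the 10% is missing.
- **Intervention**, second withdrawal criterion: "the patient meets a newly developed or not previously recognized exclusion criterion that precludes further study participation".

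Two further facts fix the timing. Randomization and blinding states: "After the run-in period, the patients will be randomized to one of the two arms". Study powder is taken only after that. Primary and secondary outcomes has every variable measured at baseline and at the end of the study, with no visit in between. The article names no per-protocol set to which the compliance rule could belong.

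**The concern.** Adherence to the powder is a post-randomisation variable. It can depend on tolerability, on perceived benefit and on how the disease is going, and any of these may differ by arm. Randomisation protects the comparison of everyone allocated; it does not protect the comparison of those who went on to comply. A rule that takes non-compliers out of the study therefore replaces the ITT comparison with a complier comparison, while the report would still carry the ITT label.

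The timing of removal does not rescue it. If a woman is removed before week 8, the only post-baseline measurement is lost unless follow-up continues after removal. If she is removed when packages are counted at the end, her outcome has been collected and is then thrown away.

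The broken sentence adds a second problem. It can be read as missing at least 10% of the powder or as taking at least 10%, and these two readings remove very different numbers of women.

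**Working it through.** **1. The statements side by side.**

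| Question | Study design / Data management | Intervention |
|---|---|---|
| Who is analysed? | ITT, including those who withdraw for any reason | Non-compliers are removed from the study |
| Who is followed to week 8? | All participants | Not those removed |
| When is the deciding variable observed? | At allocation | After randomisation, by package count |

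Both columns can hold only if removal from the study means neither loss of follow-up nor loss from the analysis, and the article does not say that.

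**2. What the 10% could mean.** Inputs from Intervention: two intakes a day for 8 weeks. Assumption: one package per intake, since package contents are not given.

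- Packages: 2 × 7 × 8 = 112; 10% is 11.2.
- Threshold read as missing at least 10%: 12 missed packages, or 12 / 2 = 6 days of intake, lead to removal. Ordinary lapses could reach this.
- Threshold read as having to take at least 10%: a woman would have to leave more than 90% untaken before removal, so almost nobody is removed.

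**3. Arm size.** Sample size gives 19 per group, raised for 15% drop-out: 19 × 1.15 = 21.85, rounded up to 22. This reproduces the plan's figure and is the arm size used below.

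**4. Possible bias, simple bound.** Suppose a fraction f of one arm is removed and its mean outcome is k SD worse than that of the women who stay. The full-arm mean is (1 − f)·m + f·(m + k) = m + f·k, where m is the mean of those who stay. Removal therefore shifts the arm mean by f·k SD. For f = 5% to 20% and k = 0.25 to 1, the shift runs from 0.05 × 0.25 = 0.0125 SD to 0.20 × 1 = 0.20 SD.

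**5. Possible effect on type I error.** Simulation with assumed inputs: no true effect, 22 per arm, normal outcome with SD 1, exclusion in the gum arm only with log-odds rising by 1 per SD of worse outcome, unadjusted two-sample t-test at 5% two-sided, 20,000 replicates.

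| Excluded in gum arm | Shift in estimate | Type I error |
|---|---|---|
| 5% | 0.05 SD | about 5% |
| 10% | 0.09 SD | about 6% |
| 15% | 0.13 SD | 6.7% |
| 25% | 0.21 SD | about 10% |

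With the same mechanism in both arms the shift is about zero. With half the dependence on outcome (log-odds 0.5) in the gum arm only, 15% exclusion gives about 0.07 SD. In the tabulated cases the removed women are the worse ones in the gum arm, so the bias favours the gum. The opposite dependence would reverse the sign.

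**The case against.** The best defence is that exclusion from the study is not stated to be exclusion from the analysis. Data management promises 8-week follow-up of everyone and ITT for all who withdraw. If packages are counted only at week 8, the outcome exists. An analysis plan not shown here may also define sets or handle missing values. Both powders are described as odourless, tasteless and identically packaged, which makes differential adherence less likely.

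Part of this stands. Lost outcomes are not certain, and bias is not certain. But the compliance rule acts on study membership, and nothing in the article limits it to a secondary analysis set. Blinding reduces differences in adherence but does not rule out differences driven by tolerability or response.

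A reader might infer three stronger points that the document does not support.

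- *That withdrawing newly ineligible women itself contradicts ITT.* It does not: Data management brings withdrawals for any reason into the ITT analysis. Only a tension remains, between ending participation under the second criterion and following everyone for 8 weeks.
- *That women who lose weight on the gum would be removed as newly ineligible.* The criterion in Eligibility, "have a history of weight loss or dieting in the last 6 months", reads most naturally as a look-back at screening. Primary and secondary outcomes lists weight change as a covariate and anthropometric indices as outcomes, so weight change on study is expected and analysed.
- *That compliance exclusions eat into power beyond the 15% allowance.* Sample size does not break that allowance down by cause, so nothing shows that they were left out. No SD is stated either. Any power figure needs one back-solved from 19 per group for LDL, which the outcomes section lists as secondary.

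**Conclusion.** The point holds for the compliance rule. As written, it removes randomised women on a variable observed after randomisation. This conflicts with the ITT commitment in Study design and Data management and with follow-up of all participants to week 8. It is a stated rule rather than a detail left to another document, and its threshold cannot be applied as written.

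The size is conditional. Under one-sided, outcome-dependent exclusion the distortion is negligible to small at 5-10% exclusion and becomes material at 15-25%, where type I error is 6.7% to about 10%. It is near zero if the mechanism is equal across arms. These figures rest on an assumed mechanism and do not predict what will happen in this trial. The case for change rests on the contradiction and on the fact that a missed week-8 measurement cannot be recovered.

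For withdrawals on safety or new ineligibility, the conclusion is narrower: the wording on ending participation should be reconciled with the 8-week follow-up.

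**What to change.** In Intervention, delete the closing clause that removes non-compliant participants from the study. Then state:

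1. Every randomised woman has the week-8 measurements already scheduled, unless she withdraws consent. This includes women who are non-compliant, who stop the powder, or who are withdrawn under either criterion.
2. The primary analysis includes all randomised women as allocated.
3. The 10% sentence is completed with its direction, and the threshold serves only to define a secondary per-protocol sensitivity analysis.
4. The second withdrawal criterion is worded so that it agrees with 8-week follow-up of all participants.

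The cost is protocol wording plus a visit that is already planned. Trial status says the trial has not yet started, so the change can precede any loss of data. The one statistical downside is a slight dilution of the effect by non-adherers, which is part of what an ITT analysis estimates. The clinical rules for stopping the powder are not addressed here.

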### Sample size

Given the absence of data in this field, we sought to determine the sample size of our study based on the study of Sheu et al. [34] selected because of its similarity to our intervention. We calculated the sample size by taking into account the LDL levels. Considering a power of 90%, a 95% confidence interval, and the changes in LDL values as one of the primary outcomes (mean difference of 28.3 mg/dl between the two groups), the required sample size was calculated to be 19 for each study group. To compensate for a drop-out rate of 15% throughout the study, we increased the final sample size to 22 patients in each group.

### Primary and secondary outcomes

Primary outcomes of the study will be FPG, glycosylated hemoglobin (HbA1c), and insulin. Secondary outcomes will include the lipid profile (total cholesterol (TC), high-density lipoproteins (HDL), low-density lipoproteins (LDL), TG), high-sensitivity C-reactive protein (hs-CRP), tumor necrosis factor-α (TNF-α), interleukin-1 (IL-1), interleukin-6 (IL-6), interleukin-10 (IL-10), interleukin-17 (IL-17), lipopolysaccharides (LPS), total antioxidant capacity (TAC), malondialdehyde (MDA), oxidative stress index (OSI), total oxidant status (TOS), superoxide dismutase (SOD), glutathione peroxidase (GSH-Px), catalase (CAT), soluble receptor for AGEs (sRAGE), carboxymethyl lysine (CML), pentosidine, 8-iso-prostaglandin F2α (8-iso-PGF2α), nitric oxide (NO), tryptophan (Trp), kynurenine (KYN), cortisol, glucagon-like peptide 1 (GLP-1), receptor for advanced glycation end products (RAGE), leptin, adiponectin, ghrelin, peroxisome proliferator-activated receptor (PPAR) gene expression, brain-derived neurotrophic factor (BDNF), endothelial cell adhesion molecules, plasminogen, cluster deference 4 (CD4), cluster deference 8 (CD8), anthropometric indices, blood pressure, dietary intake, and mental health. The following variables will be considered covariates: energy intake, weight changes, and the baseline values of glycemic indices, lipid profile, LPS, inflammatory and oxidative stress biomarkers, adipokines, and parameters related to mental health and the immune system. All variables will be measured at baseline and at the end of the study.

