### Statistical analysis

SPSS version 24.0 (SPSS Inc., Chicago, IL, USA) will be applied to analyze the data. Mean ± standard deviation (SD) or median (25th–75th percentile) and frequency (percentage) will be used to present quantitative and qualitative variables, respectively. The normality of our data will be assessed with the Kolmogorov-Smirnov test. Log transformation in the cases of non-normally distributed data will be done. In order to examine differences in qualitative and quantitative baseline variables between groups, we will apply the chi-square test and the unpaired Student *T*-test, respectively. To compare quantitative variables between groups, an analysis of covariance (ANCOVA) will be performed post-intervention. For within-group comparison, we will conduct the paired sample Student’s *T*-test or its nonparametric equivalent, the Wilcoxon test. To find the percentage difference, the absolute value of the change will be divided by the average of the values and multiplied by 100 [100 × (intervention values − placebo values)/placebo values]. *P* value < 0.05 will be considered statistically significant.

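### Three co-equal primary outcomes are each tested at P < 0.05 with no success rule, so the primary claim is not held at 5% if any one of them counts

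*Protocol article*

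**What the plan says.** Under Primary and secondary outcomes, three primaries stand side by side: "Primary outcomes of the study will be FPG, glycosylated hemoglobin (HbA1c), and insulin". The same section continues: "Secondary outcomes will include the lipid profile (total cholesterol (TC), high-density lipoproteins (HDL), low-density lipoproteins (LDL), TG", and the list runs on to CD8. That makes 37 outcomes named one by one, counting endothelial cell adhesion molecules as one. Four grouped entries close it: "anthropometric indices, blood pressure, dietary intake, and mental health".

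Under Statistical analysis, the between-group test is the same for all quantitative variables: "To compare quantitative variables between groups, an analysis of covariance (ANCOVA) will be performed post-intervention". The section ends with one rule, that a P "value < 0.05 will be considered statistically significant". The Methods paragraph of the Abstract gives the same threshold. Neither place separates primary from secondary outcomes.

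Under Sample size, the calculation rests on "the changes in LDL values as one of the primary outcomes (mean difference of 28.3 mg/dl between the two groups". LDL is therefore primary in one section and secondary in another.

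**The concern.** With several co-equal primaries, a per-test threshold controls the error of the trial's conclusion only if something links the tests: a single key outcome, an order, an adjustment, or a requirement that all succeed. The protocol states the threshold and none of these links. A trial that finds one primary at P = 0.04 and the other two null could report a positive primary result, and nothing in the text would rule that out. The contradiction about LDL means that the primary family itself is not settled.

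The same threshold covers a long list of secondary outcomes in a trial of 22 women per group. The Conclusion expects the results to support use of the gum in managing diabetes and its comorbidities. Scattered significant secondary results could be presented as that support.

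**Working it through.** **Inputs.** Three primaries and 37 individually named secondaries (Primary and secondary outcomes). Threshold 0.05 per test (Statistical analysis). Sidedness is not stated outright; two-sided 5% is assumed from "Considering a power of 90%, a 95% confidence interval" (Sample size). The documents give no correlations among outcomes, so a range is shown. For the error rates, test statistics are taken as jointly normal with a common correlation and no true effect on any outcome.

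**The plan's own figure.** The plan states no overall error rate. Its 19 per group for LDL cannot be reproduced because no SD is given. From n = 2 × [(1.96 + 1.2816) × SD / 28.3]², 19 per group implies an SD of about 26.2 to 26.9 mg/dl. The error rates below do not depend on this.

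**Three primaries, any one counts.** If independent: 1 − 0.95³ = 1 − 0.8574 = 0.1426.

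| Common correlation | At least one of three, two-sided | At least one favouring the gum | At least one of four (LDL added), two-sided |
|---|---|---|---|
| 0 | 14.3% | 7.3% | 18.5% |
| 0.3 | 13.6% | 6.8% | 17.4% |
| 0.5 | 12.5% | 6.3% | 15.6% |
| 0.7 | 10.9% | 5.5% | 13.0% |
| 0.9 | 8.4% | 4.2% | 9.4% |

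The first row follows by hand: 1 − 0.975³ = 0.073 and 1 − 0.95⁴ = 0.185. The other rows come from numerical integration of the multivariate normal. The reference values for a single test are 5% two-sided and 2.5% in favour of the gum. Relative to these, the inflation for three primaries runs from 14.3/5 = 2.9 times down to 8.4/5 = 1.7 times.

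**All three required.** The chance that all three are falsely significant cannot exceed that of any one of them, so the error is at most 5%.

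**Secondaries.** Expected false positives: 37 × 0.05 = 1.85, whatever the correlation. Chance of at least one: 1 − 0.95³⁷ = 0.85 if independent, falling to about 72%, 55% and 37% at common correlations of 0.3, 0.5 and 0.7.

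**Price of an adjustment.** For an unadjusted two-sample t-test with 19 per group and 90% power, the detectable standardised difference is 1.08 SD at 0.05 and 1.24 SD at 0.05/3 = 0.0167. If LDL joins the family, Holm's first step is 0.05/4 = 0.0125 and the figure is 1.28 SD.

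**The case against.** The strongest reply is that the protocol never says that one significant primary makes the trial positive. That is correct. A reader might infer that, as written, any single result below 0.05 supports an efficacy claim, but the text sets only a per-test threshold and is silent on what counts as success. The 8 to 14% is therefore conditional on the any-one reading.

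A second reply is that test order and adjustment are often left to a statistical analysis plan, which is not shown here. This has some force as to whether a rule exists elsewhere. But the article is not merely silent: it fixes one unqualified threshold for all tests and names co-equal primaries. A later multiplicity rule would have to change that sentence.

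Third, Study design and participants describes a superiority framework, and 14% counts false differences in both directions. It should not be read as the chance of a false claim for the gum; that chance is about 4 to 7%. The inflation over 2.5% remains.

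Fourth, a reader might conclude that some false significant secondary results are almost certain. The documents do not support that. The 85% needs independence, and the protocol's own formulas rule it out for some outcomes: the oxidative stress index is computed from TOS and TAC, and LDL is calculated rather than measured. Only the expected count of about 1.9 survives correlation. Unadjusted testing of secondary outcomes is also common practice, provided that no confirmatory claim is drawn from them.

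**Conclusion.** The point holds in conditional form. Three unordered primaries, each tested at 0.05 with no rule on how many must succeed, do not hold the primary claim at 5% if any one suffices. The two-sided error is then about 8 to 14%, or about 4 to 7% against 2.5% when only results favouring the gum count. If LDL is also primary, the two-sided ceiling is 18.5%. If all three were required, the error would be at most 5%; the protocol does not say which rule applies, and that is the defect. A general statement that the error is two to three times nominal would go too far, since it is about 1.7 times at correlation 0.9.

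For the 37 individually named secondaries, about 1.9 false positives are expected under the null. The figures assume two-sided testing, jointly normal test statistics, equal correlations and no true effects.

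**What to change.** 1. Reconcile Sample size with Primary and secondary outcomes on whether LDL is primary. Until that is done the test family cannot be defined.
2. In Statistical analysis, either apply Holm across the resulting primary outcomes at an overall two-sided 5%, or fix a test order before data are seen.
3. In the same section, state that no confirmatory efficacy claim rests on secondary outcomes.

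All three are changes of wording. Trial status says that the trial has not yet started, so on that account they can be made before outcome data exist.

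The cost is power. With Holm on three primaries, the smallest P must be below 0.0167, which raises the effect detectable with 90% power from about 1.08 to 1.24 SD at 19 per group. That is a t-test approximation; the planned ANCOVA with baseline adjustment would give different values. A fixed order costs nothing for the first outcome, but later outcomes can be tested only if those before them succeed.
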